## Study Protocol

|                    |                                                                                                                                                                                                                                                                                                                                                                                                                                                                                                                                                                                                                                 |
|--------------------|---------------------------------------------------------------------------------------------------------------------------------------------------------------------------------------------------------------------------------------------------------------------------------------------------------------------------------------------------------------------------------------------------------------------------------------------------------------------------------------------------------------------------------------------------------------------------------------------------------------------------------|
| Study Title        | Multi-dimensional cell-free DNA-based liquid biopsy for sensitive early detection of gastric cancer                                                                                                                                                                                                                                                                                                                                                                                                                                                                                                                             |
| Number of Sites    | Single site                                                                                                                                                                                                                                                                                                                                                                                                                                                                                                                                                                                                                     |
| Rationale          | Gastric cancer remains as one of the leading causes of death worldwide. Detecting gastric cancer earlier is vital for managing the disease effectively, improvement of survival rates and reduction of morbidity. Blood-based liquid biopsy has emerged as a promising technology for the early detection of multiple types of cancer, which can complement traditional cancer screening methods in a non-invasive manner. We developed a novel liquid biopsy assay using multi-dimensional cell-free DNA (cfDNA) features from whole genomic sequencing (WGS) data for the detection of gastric cancer at early stages.        |
| Study Design       | A single-center prospective observational study will be used to develop and valid the gastric cancer early detection study. The study is divided into two phases. The first phase of the study will enroll ~250 participants, including ~100 stage I-II gastric cancer patients and ~150 non-cancer individuals, over a period of 8 months. The cfDNA profiles of these participants will be used to develop a multi-layer machine learning model for identifying cancer presences. The second phase of the study will enroll ~125 participants over a period of 4 months to validate the performance of the cfDNA-based assay. |
| Primary Outcomes   | The area under the receiver operator characteristic curve (AUROC) metric for differentiating stage I/II gastric cancer patients and non-cancer individuals using the cfDNA-based assay.                                                                                                                                                                                                                                                                                                                                                                                                                                         |
| Secondary Outcomes | The sensitivity and specificity for differentiating stage I/II gastric cancer patients and non-cancer individuals using the cfDNA-based assay.                                                                                                                                                                                                                                                                                                                                                                                                                                                                                  |
| Interventions      | Not applicable                                                                                                                                                                                                                                                                                                                                                                                                                                                                                                                                                                                                                  |
| Number of Samples  | First phase: ~100 stage I-II gastric cancer patients, ~150 non-cancer individuals.                                                                                                                                                                                                                                                                                                                                                                                                                                                                                                                                              |

|                    |                                                                                                                                                                                                                                                                                                                                                                                                                                                                                                                                                                                                                                                                                                                                                                                                                                                                                                                                                                                          |
|--------------------|------------------------------------------------------------------------------------------------------------------------------------------------------------------------------------------------------------------------------------------------------------------------------------------------------------------------------------------------------------------------------------------------------------------------------------------------------------------------------------------------------------------------------------------------------------------------------------------------------------------------------------------------------------------------------------------------------------------------------------------------------------------------------------------------------------------------------------------------------------------------------------------------------------------------------------------------------------------------------------------|
|                    | Second phase: ~50 stage I-II gastric cancer patients, ~75 non-cancer individuals.                                                                                                                                                                                                                                                                                                                                                                                                                                                                                                                                                                                                                                                                                                                                                                                                                                                                                                        |
| Procedure          | This prospective study collects blood samples from participants with a new diagnosis of cancer (cancer arm) and from participants who do not have a diagnosis of cancer (non-cancer arm) to develop and validate the cfDNA-based assay for the early detection of gastric cancer.                                                                                                                                                                                                                                                                                                                                                                                                                                                                                                                                                                                                                                                                                                        |
| Inclusion Criteria | 
Inclusion criteria for all the participants:
 
 
• 18 – 85 years old.
 
• Individuals without a prior history of cancer.
 
• Individuals with a plasma sample that was collected before initial screening tests and passed quality control (QC).
 
• Individuals who provided informed consent.
 
 
Inclusion criteria for cancer arm participants:
 
 
• Individuals who were pathologically confirmed with gastric adenocarcinomas by biopsies without concomitant malignancies and received curative surgeries for gastric cancer.
 
 
Inclusion criteria for non-cancer arm participants:
 
 
• Individuals who showed no signs of cancers based on routine physical examinations, including blood tests, ultrasound and CT, and no sign of gastric cancer from gastric cancer-specific screening tests.
 
 |
| Exclusion Criteria | 
Exclusion criteria for all the participants:
 
 
• Individuals who withdrew informed consent.
 
• Individuals whose sequencing data failed QC.
 
 
Exclusion criteria for cancer arm participants:
 
 
• Individuals who were pathologically confirmed with stage III/IV gastric cancer.
 
 
Exclusion criteria for non-cancer arm participants:
 
 
• Individuals with significant chronic diseases of other systems, such as severe cardiovascular diseases, uncontrolled diabetes, hypertension, and infectious diseases.
 
                                                                                                                                                                                                                                                                                               |

|                      |                                                                                                                                                                                                                                                                                                                                                                                                            |
|----------------------|------------------------------------------------------------------------------------------------------------------------------------------------------------------------------------------------------------------------------------------------------------------------------------------------------------------------------------------------------------------------------------------------------------|
|                      | 
 
Individuals who had abnormal results of tumor marker (CEA, CA19-9, CA125, PSA, AFP, etc.) examinations within the past year.
 
                                                                                                                                                                                                                             |
| Sample Enrollment    | The study will enroll participants who voluntarily register in this clinical study at Zhejiang Cancer Hospital. All participants will be pre-screened as per Inclusion and Exclusion Criteria.                                                                                                                                                                                                             |
| Test                 | Blood samples will be collected and processed at Zhejiang Cancer Hospital.                                                                                                                                                                                                                                                                                                                                 |
| Statistical Analysis | The comparison of continuous numeric data will be conducted using the Wilcoxon test. The comparison of proportions between groups will be conducted using the Fisher's exact test. The trend of continuous numeric data across ordered groups will be assessed using Jonckheere trend test. A two-sided P value of less than 0.05 will be considered significant for all tests unless otherwise indicated. |
| Overall Duration     | Estimated about 12 months                                                                                                                                                                                                                                                                                                                                                                                  |

## 1 INTRODUCTION

### 1.1 Introduction

Gastric cancer is one of the major global health challenges and leading causes of death. Worldwide, it is estimated that 1,089,103 people were diagnosed with gastric cancer and 768,793 deaths from gastric cancer occurred in 2020(1). Unfortunately, 62% of gastric cancers are detected after the cancer has already spread, either regionally or distantly, resulting in limited treatment options and poor prognosis. Patients with advanced-stage gastric cancer have an extremely low 5-year survival rate of 6%. However, if gastric cancer is diagnosed and treated at early stages before dissemination, the 5-year survival rate is 72%(1). Therefore, there is a need for optimized tools to detect gastric cancer earlier in order to manage the disease effectively, improve survival rates, and reduce morbidity.

Currently, there are a few screening tests available for gastric cancer, such as gastroscopy, computed tomography, Barium Swallow X-ray, *Helicobacter pylori* Antibody Test etc. However, these conventional methods are limited by high cost, invasiveness, poor compliance, or

relatively low accuracy. A cost-effective, non-invasive, and accurate assay is highly desired for regular screening for gastric cancer.

Cell-free DNA (cfDNA)-based liquid biopsy has emerged as a promising technology for the early detection of gastric cancer, offering a non-invasive complement to traditional cancer screening methods. Unlike conventional screening and tissue biopsy, cfDNA-based liquid biopsy only requires a blood sample, making the process quicker and more convenient. cfDNA consists of fragmented genomic DNA released into the bloodstream through mechanisms such as apoptosis, necrosis, and secretion. Tumor-derived cfDNA, known as circulating tumor DNA (ctDNA), carries genetic and epigenetic aberrations characteristic of cancer, including mutations, copy number alterations, aberrant methylation, and abnormal fragmentation. Through next-generation sequencing and computational algorithms, ctDNA can be distinguished from the total pool of cfDNA, enabling the accurate early detection of gastric cancer.

We have preliminarily assessed the efficacy of various cfDNA characteristics, including fragment size pattern (FSP), copy number variation (CNV), nucleosome coverage pattern (NCP), and single nucleotide substitutions (SNS), in detecting gastric cancer signals. In this study, our goal is to develop a cfDNA-based liquid biopsy assay that leverages multi-dimensional cfDNA features profiled from low-depth whole-genome sequencing data to accurately identify gastric cancer at early stages.

## **1.2 Purpose**

1st Phase – Assay development and preliminary validation:

The objective of the first phase is to design, develop, and internally validate a cfDNA-based liquid biopsy assay optimized for the precision of identifying early-stage gastric cancer patients from non-cancer individuals. This phase also aims to determine a clinically meaningful threshold that effectively balances sensitivity and specificity.

2nd Phase – Assay validation:

The objective of the second phase is to collect samples to independently validate the performance of the assay developed in the first phase.

## **2 STUDY OBJECTIVES**

### **2.1 Primary Objectives (Primary Outcomes)**

1st Phase – Assay development and preliminary validation:

- Utilize the data collected in this phase to comprehensively profile cfDNA characteristics.
- Develop a classification model to distinguish gastric cancer patients from non-cancer individuals.
- Conduct five-fold cross validations to assess the assay's efficacy and calculate the AUROC metric for binary classification.

2nd Phase – Assay validation:

- Use the assay developed in the 1st phase to predict the cancer presences in the participants enrolled in this phase and calculate the AUROC metric for the predictions.

## **2.2 Secondary Objectives (Secondary Outcomes)**

1st Phase – Assay development and preliminary validation:

- Establish an appropriate threshold that maximize Youden's index from cross validations.
- Calculate the sensitivity and specificity of the assay at this threshold.

2nd Phase – Assay validation:

- Calculate the sensitivity and specificity of the assay at the predefined threshold from the 1st phase.

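### The Phase 2 cut-off is locked at a cross-validated Youden maximum, which moves with the random fold split if run once; the median cut-off over repeated splits is steadier at no cost in participants

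*Protocol*

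**What the plan says.** Protocol section 2.1 sets the Phase 1 evaluation: "Conduct five-fold cross validations to assess the assay's efficacy and calculate the AUROC metric for binary classification". Section 2.2 then derives the cut-off from the same exercise, again named in the plural: "Establish an appropriate threshold that maximize" Youden's index. For Phase 2 it carries that cut-off forward unchanged: "Calculate the sensitivity and specificity of the assay at the predefined threshold from the 1 st phase".

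The synopsis gives the sizes: "First phase: ~100 stage I-II gastric cancer patients, ~150 non-cancer individuals" and "Second phase: ~50 stage I-II gastric cancer patients, ~75 non-cancer individuals". It lists AUROC as the primary outcome, and sensitivity and specificity as secondary outcomes. Section 1.2 makes finding a usable cut-off one of the aims of Phase 1.

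The protocol does not say whether the five-fold procedure is run once or several times, or how cut-offs from several runs would be combined. It gives no expected AUROC, sensitivity or specificity, no number of features, and no model beyond a general description. A statistical analysis plan may exist but is not at hand.

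**The concern.** The empirical Youden index is a step function of about 250 out-of-fold scores. Its top is usually broad and ragged, so a small change in the scores can move the location of the maximum a long way. The scores change whenever participants are dealt into folds differently. The AUROC averages over all cut-offs and barely notices; the position of the peak does.

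That position is the one Phase 1 number that determines both Phase 2 secondary outcomes. With a single run, another seed on the same 250 people could lock a noticeably different trade-off between sensitivity and specificity. A Phase 2 confidence interval at the locked cut would not show this. An unspecified split also leaves room to choose a seed that flatters the Phase 1 sensitivity and specificity reported at the same cut-off.

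**Working it through.** **Inputs from the protocol.** Phase 1 has about 100 + 150 = 250 participants and Phase 2 about 50 + 75 = 125; both totals agree with the Study Design row of the synopsis. The rule is the Youden maximum from five-fold cross-validation, then locked. There is no stated precision or performance figure to reproduce.

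**Assumptions.** Gaussian features; stratified five-fold splits; the cut t* maximises sensitivity(t) + specificity(t) − 1 on the pooled out-of-fold scores; t* is applied to the model refitted on all 250; true specificity at t* is computed for new participants. Set A used ridge logistic regression (20 to 500 features, 20 to 25 splits per data set) and random forests (50 features, 10 splits). Set B used ridge logistic regression with 40 features. Set C used 40 features, 10 of them informative, with 40 data sets and 15 seeds each.

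**Size of the split effect.** Split-only SD = √(mean over data sets of the variance across splits). The comparison is the Phase 2 binomial standard error (SE), √(s(1 − s)/75), at the mean specificity s of the same scenario. For example, at s = 0.791 it is √(0.791 × 0.209/75) = 4.7 points. Set A gives:

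| Model | AUROC | Mean specificity (%) | Split-only SD (points) | Binomial SE (points) | Ratio |
|---|---|---|---|---|---|
| Ridge, 20 features | 0.771 | 70.3 | 8.0 | 5.3 | 1.5 |
| Ridge, 500 | 0.780 | 69.9 | 7.4 | 5.3 | 1.4 |
| Ridge, 100 | 0.832 | 75.5 | 6.4 | 5.0 | 1.3 |
| Forest, 50 | 0.841 | 77.6 | 5.6 | 4.8 | 1.2 |
| Ridge, 500 | 0.865 | 79.1 | 5.4 | 4.7 | 1.1 |
| Forest, 50 | 0.925 | 83.5 | 4.3 | 4.3 | 1.0 |
| Ridge, 100 | 0.930 | 85.6 | 3.4 | 4.1 | 0.8 |
| Ridge, 500 | 0.968 | 89.9 | 2.7 | 3.5 | 0.8 |
| Forest, 50 | 0.981 | 93.3 | 2.0 | 2.9 | 0.7 |

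Set B gives 8.4, 6.3, 3.6 and 2.2 points at AUROC 0.76, 0.85, 0.94 and 0.98. Set C gives 6.3 at 0.81 and 4.6 at 0.90. All three follow the same gradient. Single data sets vary widely around it: 3.1 to 8.3 points at AUROC 0.865. Sensitivity moves by a similar amount (5.8 points at 0.865, 3.6 at 0.930).

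**What repeats achieve.** If the cut-off is averaged over R repeats, the split variance should fall to about 1/R and the variance from who was sampled should remain. At AUROC 0.865 the total SD with one run is 6.1 points, so the sampling part is 6.1² − 5.4² = 8.05. With R = 20 the expected total SD is √(8.05 + 29.16/20) = 3.1 points, which is what the simulation gave. Other Set A results for the averaged cut-off: 7.4 to 4.1 points (AUROC 0.832), 4.1 to 2.5 (0.930) and 3.4 to 2.2 (0.968).

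The median of 20 cut-offs also works:
- Total SD in Set B: 9.6 to 5.2, 6.6 to 3.7, 4.2 to 3.4 and 3.8 to 2.6 points at AUROC 0.76, 0.85, 0.94 and 0.98.
- Split-only SD in Set C: 6.3 to 1.9 points (AUROC 0.81) and 4.6 to 1.3 (0.90).
- Split SD of the Phase 1 AUROC in Set C: 0.012 to 0.003 and 0.008 to 0.002.

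**The combining rule matters.** One Youden cut on scores averaged over repeats still has a ragged peak. Its SD across data sets was 5.6 against 6.1 for one run (AUROC 0.865), 7.1 against 7.4 (0.832) and 3.7 against 3.4 (0.968). It helped clearly only at AUROC 0.780 (5.9 against 8.1), where averaging the cut-offs did better (3.7).

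**The case against.** The strongest reply is that the number of repeats, the seeds and the combining rule commonly belong in the analysis plan, which is not shown, and that the plural in sections 2.1 and 2.2 may already mean repeated runs. Both points stand. The protocol does not fix a single run, and silence about repeats is not in itself an error. What remains is that the protocol does fix the rule on which two Phase 2 outcomes depend, and that a steadier version of it is available almost free.

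Four stronger readings are tempting but not supported.

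- A reader might infer that Phase 2 sensitivity and specificity are biased, or that a seed could be tuned to them. Section 2.2 has the cut-off settled in Phase 1, so the Phase 2 estimates are valid for whatever cut is locked. Seed choice can flatter only the Phase 1 figures.
- A reader might take 5 to 6 points as the general size. It holds at AUROC of roughly 0.84 to 0.87, and the protocol states no AUROC.
- A reader might set a 6-point SD beside the 3.5-point SE at 90% specificity and call the split effect nearly twice the sampling error (6/3.5 = 1.7). That mixes a weaker assay with a better one. Matched within scenario, the ratio runs from 1.5 at AUROC 0.77 to below 1 from about 0.93.
- A reader might say that repeats remove the problem. They average out the split component only. The variation from which 250 people are enrolled stays, and so does the Phase 2 binomial error.

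It is also fair that the split mostly slides the operating point along the ROC curve. The gain in Youden's index from the median cut-off is small: 0.003 to 0.009 in Set B and about 0.01 in Set C.

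**Conclusion.** The point holds as a cheap improvement to the threshold rule. If the cross-validation is a single run, the operating point carried into Phase 2 is unstable. The split-only SD of true specificity is about 8 points at AUROC 0.76 to 0.78, 5 to 6 at 0.84 to 0.87, 3.5 to 4 at 0.93 to 0.94 and about 2 at 0.98. Up to an AUROC of about 0.93 that is comparable to the Phase 2 binomial SE of 4.6 to 3.5 points (75 controls, 80% to 90% specificity). Above that it is the smaller of the two.

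These sizes rest on the assumed AUROC, Gaussian features, the simulated classifiers, and a cut taken on pooled out-of-fold scores and applied to a refitted model. The consequence is an arbitrary element in two secondary outcomes and some freedom in the Phase 1 figures. The primary Phase 2 AUROC uses no cut-off and is not affected.

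**What to change.** In section 2.1, specify stratified five-fold cross-validation repeated at least 20 times with seeds set in advance, and report the mean AUROC over repeats. In section 2.2, take the Youden cut-off within each repeat and lock the median of those cut-offs as the Phase 2 threshold. State explicitly that it is not a single Youden cut on averaged scores. Report Phase 1 sensitivity and specificity at that locked cut-off over all the repeats, so that no single split can be singled out. If the analysis plan already says this, a cross-reference is enough.

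The cost is computing time: 5 × 20 = 100 fold fits in place of 5, about 20 times the model fitting. No participants, samples or sequencing are added. In the simulations at AUROC 0.85 to 0.87, the total SD of true specificity falls from about 6 to 6.6 points to about 3 to 3.7. The remainder, due to the size of Phase 1, is not something this change can reduce.

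### Phase 1 sensitivity and specificity are read at the cut-off that maximises Youden's index, apparently on the same cross-validated predictions, so these secondary outcomes are modestly optimistic on average

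*Protocol*

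**What the plan says.** Section 2.2 lists two Phase 1 secondary outcomes in sequence. The first is to "Establish an appropriate threshold that maximize Youden's index from cross validations". The second is to "Calculate the sensitivity and specificity of the assay at this threshold".

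The only Phase 1 evaluation scheme is in section 2.1: "Conduct five-fold cross validations to assess the assay's efficacy and calculate the AUROC metric for binary classification". No inner loop, Phase 1 hold-out set or optimism correction is stated for the threshold. Section 1.2 gives the aim of the phase as to "design, develop, and internally validate a cfDNA-based liquid biopsy assay", and the phase is headed as development and preliminary validation.

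The synopsis gives the sizes as "First phase: ~100 stage I-II gastric cancer patients, ~150 non-cancer individuals" and "Second phase: ~50 stage I-II gastric cancer patients, ~75 non-cancer individuals". In Phase 2, section 2.2 asks to "Calculate the sensitivity and specificity of the assay at the predefined threshold from the 1 st phase", on newly enrolled participants.

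**The concern.** Cross-validation keeps each participant's score independent of the model fit that produced it. It does not keep the cut-off independent of the scores. If one cut-off is picked because sensitivity plus specificity is largest on a set of predictions, and the two proportions are then reported from that set, chance fluctuations that favoured the chosen cut-off are counted as performance.

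What is at stake is limited but real. Sensitivity and specificity are named outcomes for Phase 1 in their own right, under a phase that claims internal validation. A reader would take them as honest estimates of how the assay performs at its threshold. Followed as written, the plan makes them too favourable on average, and part of any fall from Phase 1 to Phase 2 would come from the method.

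**Working it through.** **Inputs.** From the protocol: 100 cases and 150 controls in Phase 1 (100 + 150 = 250, as stated), 50 and 75 in Phase 2 (50 + 75 = 125, as stated), the Youden rule, and five-fold cross-validation. The protocol gives no target AUROC, sensitivity or specificity, so it has no performance figure to reproduce. The true AUROC is therefore an assumption, taken over 0.80 to 0.95.

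**Direction.** Let J(c) = Se(c) + Sp(c) − 1 be the true index at cut-off c, Ĵ(c) its estimate, c* the best true cut-off and ĉ the one chosen from the data. In every data set Ĵ(ĉ) ≥ Ĵ(c*), because ĉ maximises Ĵ. Since c* is fixed, Ĵ(c*) is unbiased for J(c*), and J(c*) ≥ J(ĉ). Hence E[Ĵ(ĉ)] ≥ J(c*) ≥ E[J(ĉ)]. The bias is upward in expectation, though a single study can go the other way.

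**Size.** Scores were simulated as normal with unit variance and mean shift d = √2 · z(AUROC), with 20,000 data sets per AUROC. In each, the empirical Youden cut-off was found, and the proportions at that cut-off were compared with their true values there. Biases are in percentage points and were taken before rounding.

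| Assumed AUROC | Reported Se / Sp (%) | True Se / Sp at chosen cut-off (%) | Bias Se | Bias Sp | Bias J |
|---|---|---|---|---|---|
| 0.80 | 74.3 / 74.2 | 71.4 / 72.3 | 2.9 | 1.9 | 4.8 |
| 0.85 | 78.6 / 78.4 | 75.9 / 76.6 | 2.6 | 1.8 | 4.4 |
| 0.90 | 83.1 / 83.3 | 80.8 / 81.7 | 2.3 | 1.6 | 3.9 |
| 0.95 | 89.0 / 89.0 | 87.0 / 87.7 | 2.0 | 1.3 | 3.3 |

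At 0.90 the two steps of the inequality can be seen. Reported J is 0.831 + 0.833 − 1 = 0.664, the best attainable J is 0.635, and true J at the chosen cut-off is 0.808 + 0.817 − 1 = 0.625. The gap is (0.664 − 0.635) + (0.635 − 0.625) = 0.029 + 0.010 = 0.039. Across the table, the reported index exceeded the true one in about 81 to 82% of simulated studies.

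**Scale against sampling error, at AUROC 0.90.**
- Sensitivity: √(0.808 × 0.192 / 100) = 0.039, so the bias is 2.3 / 3.9 ≈ 0.6 of a standard error.
- Specificity: √(0.817 × 0.183 / 150) = 0.032, so the bias is 1.6 / 3.2 = 0.5 of a standard error.
- Phase 1 minus Phase 2 sensitivity: √(0.808 × 0.192 × (1/100 + 1/50)) = 0.068, or 6.8 points.

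**Against the locked model.** The table compares like with like: the scores that were cross-validated. The assay carried into Phase 2 would be refitted on all Phase 1 data, while each fold model is trained on about 80% of it. The refitted model tends to perform a little better, which offsets part of the optimism. Measured against it, the overstatement of J is about 2 to 3 points. That figure is rougher, because it depends on the model and the number of features.

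**Does the remedy work?** With the cut-off chosen on four folds and scored on the fifth (4,000 data sets), estimated against true sensitivity/specificity was 0.715/0.721 against 0.714/0.721 at AUROC 0.80, 0.806/0.817 against 0.807/0.817 at 0.90, and 0.870/0.875 against 0.870/0.875 at 0.95. The optimism from choosing the cut-off is removed. This run holds the scores fixed, so it tests threshold selection only, not model tuning.

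**The case against.** The strongest reply is that the design already contains the main safeguard. The threshold is locked after Phase 1 and applied to new participants in Phase 2, and Phase 1 is labelled preliminary. That stands, and it keeps the point modest. It does not correct the Phase 1 outcomes, which are listed separately and would be reported as they come.

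A second reply is that the protocol never says the predictions are pooled or that the same ones are used twice. Such mechanics are often left to a statistical analysis plan, which is not at hand. It is fair to say that the same-data step is a reading and not a stated fact. But section 2.2 itself fixes the selection rule and the evaluation at that threshold, and no other Phase 1 data are named for the evaluation.

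Three stronger readings are tempting and are not supported:

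- A reader might infer that Phase 1 confidence intervals would sit too high. The protocol specifies no such intervals.
- A reader might infer that the drop to Phase 2 would count as failed replication. No replication criterion is set, and a 2.3-point effect is well inside the 6.8-point standard error of the difference.
- A reader might quote nearly 5 points as confirmed by fitted models. A five-fold ridge-logistic check did give overstatements in J of 2.7, 2.9 and 4.9 points. Under the equal-variance normal model, J = 2Φ(d/2) − 1 and AUROC = Φ(d/√2), so its true J values of 0.574, 0.361 and 0.162 correspond to AUROC of about 0.87, 0.75 and 0.61. The 4.9 comes from a near-useless classifier. The one case inside the assumed range gave 2.7. Youden's index also adds two errors together and is not itself a listed outcome.

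**Conclusion.** The point holds in a limited form. On the natural reading of section 2.2, the Phase 1 sensitivity and specificity are optimistic on average, by about 2 to 3 and 1 to 2 percentage points respectively. This is roughly half a binomial standard error for each.

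The size rests on an assumed true AUROC of 0.80 to 0.95, equal-variance normal scores, and arms of 100 and 150. The direction does not depend on those assumptions, but it does depend on the same predictions being used to choose and to score the cut-off.

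It would be wrong to extend the point to the primary outcome, since AUROC uses no threshold, or to Phase 2, where the threshold is fixed before the data are seen.

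**What to change.** For the Phase 1 figures, choose the threshold, together with any feature selection and tuning of the multi-layer model, inside the training folds, and score sensitivity and specificity on the held-out fold. A bootstrap optimism-corrected estimate is an acceptable alternative.

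Keep the present plan of deriving one threshold from all Phase 1 data and locking it for Phase 2. If same-data Phase 1 figures are still shown, label them as apparent and point to the Phase 2 figures as the estimates of performance at the locked threshold. If the intended method already separates choice and scoring of the cut-off, one sentence in section 2.2 saying so settles the matter.

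The cost is analysis code and wording, and Phase 1 figures a few points less favourable. The held-out figures describe the threshold-setting procedure on about four fifths of the data and not the single locked cut-off, so they may be slightly pessimistic for the final assay. No participants, samples or timelines change.
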